### Intervention delivery

Participants in the treatment group will be administered Cogmed ™ (RM version) program. Developed for children aged 7 years and above, it is a commercially available [72] online adaptive working memory training program. For the purpose of this study, participants will train on the standard protocol consisting of a total 25 training blocks to be completed over a span of 5 weeks. Participants will be required to complete one training block in 50 min every day for 5 days a week for 5 weeks. Each training block includes a series of interactive and adaptive exercises that not only targets but also dynamically adapt to the visuo-spatial and verbal WM ability of the participants at the time of the training. During the training, if the participant makes consecutive errors on four trials, the program will automatically enforce a mandatory break for 15 s. At the completion of each training block, the participant gets rewarded with a reward game, RoboRacing.

Cogmed training will be completed online by the participants from their homes. It will be supervised by a trained Cogmed Coach who is the study co-ordinator. Once the participants are randomized to the treatment group, the Cogmed Coach will conduct a Start-up session with the participants and their Training Aides. In this session, the Cogmed Coach will (a) provide an information sheet to set up the program on the home computer or iPad, (b) explain the training structure, (c) plan the training times (d) discuss participants’ motivation and expectations, (e) discuss reward system, (f) schedule online weekly meetings, and (g) fill out the Cogmed Questionnaire. Online meetings (through Skype Business/Google Hangouts/GoTo Meetings) will be held once per week for 5 weeks of training to provide support and answer any queries.

The training performance and compliance will be monitored through a secure server by the Coach.

The program requires internet access and if necessary families will be provided with an internet-connected iPad for the duration of the program. The coach can monitor the training and compliance by logging into a secure server. Program compliance can be assessed as the number of sessions completed by each child, and time spent per session will be recorded.

### Implementation of active control*:* Lexia Reading Core5

Participants in the active-control group will be administered commercially available Lexia Reading Core5 [73, 74]. An adaptive computerized reading program, Lexia battery caters for all age groups of children but has no memory training component. Consisting of a total 18 level and 89 activities, it delivers structured, in-depth, and individualized training in six areas of reading – Phonological Awareness, Structural Analysis, Vocabulary, Phonics, Fluency, and Comprehension. Each participant will first complete 20 min of auto-placement on their initial log-in to Lexia Reading Core5. Auto-placement is a tool that assesses participant’s current level of functioning. Based on this performance, participants will be assigned an appropriate program level for their training. Once participants successfully complete a prescribed set of units, they will progress to higher levels of the program. In addition to the online training, Lexia also provides supplementing individualized paper-based practice materials for participants struggling on a particular activity. On successful completion of a level, the participant is rewarded with a certificate. Participants will train on Lexia Reading Core5 for 50 min each day for 5 days a week for 5 weeks at their homes.

The Lexia program provides an active- control for the experience of sitting in front of a computer and engaging with fun learning tasks randomized to the participants in the active-control group. As with Cogmed, the coach will provide assistance with the set-up and weekly online meetings.

### Technology

Since this RCT uses online training programs and online clinician support, internet enabled iPads will be provided to the participants with no access to a computer. Technical issues faced by the participant will be addressed by the project co-ordinator in the online weekly meetings.

### Facilitator training and program fidelity

The Chief Investigator and the study co-ordinator were trained in administration and use of Cogmed and Lexia. Program fidelity will be monitored through the Coach’s weekly online meetings with families.

### Study measures

The participants will be screened for eligibility in a neuropsychological assessment (approximately 1–2 h). If the child is found eligible for the intervention study, questionnaires covering background and demographic information as well as behavioural function, will be completed by parents/guardians (approx. 1.5–2 h) and the teacher. The study measures are all widely-used, standardised tests and questionnaires appropriate for the target age group, and have established reliability and validity. Details pertaining to the participant’s injury (e.g., date of injury, age at injury, diagnosis, Glasgow Coma Score, neurological signs) are extracted from the hospital database. The parents/guardian provides the demographic information.

WM and DM of the participants are the two primary outcomes for this study. Automated Working Memory Assessment (AWMA) [75] is a validated computerized measure of WM skills, is used for assessing WM. AWMA- Short (AWMA-S) comprises of four sub-tests, namely, Listening Recall (verbal WM), Spatial Recall (visuo-spatial WM), Digit Recall (verbal short-term memory), and Dot Matrix (visuo-spatial short-term memory). In this battery, WM tasks involve both storage and processing of information whereas short-term memory tasks involve storage with minimal processing.

DM is measured using an experimental digital task that has been conceptualised on the basis of a previous research study [34]. Initially, the child is presented with everyday scenarios for example, purchasing a book. They are presented with different aspects related to that scenario, for example, cost of the book. Then they are asked to identify from choices presented on an information board what they feel is most important in making that decision. In order to reach the final decision in a situation, information acquisition is a key process in DM. Therefore, by understanding how children process information in this task, this study purports to further the knowledge of underlying cognitive processes involved in DM.

Secondary outcomes include functional measures of academic achievement, social, behavioural, and quality of life outcomes. Parent and teacher report measures will be administered to assess social and behavioural status, and quality of life outcomes.

### Participant flow and estimated sample size

This study will recruit 74 eligible participants and randomize 37 participants each in the treatment group and the active-control group. This estimated sample size is in accordance with our power calculation so that a clinically significant difference can be found between the treatment group and the active-control group. Sample size calculations were based on the ability to detect a statistically significant difference of 0.8 SD between the treatment group and an active control group based on Automated Working Memory Assessment, with a significance level of 0.05 and power of 0.80 (Fig. 3).

**Fig. 3 Fig3:**
[figure not shown]
Represents the estimated participant flow and sample size

### Data storage

Data will be collected in both pen-paper and digital format and securely stored at MCRI. Only this study’s chief investigators will have access to the collected data, both throughout and after the conclusion of the study.

### Data analysis

This RCT will follow the intention-to-treat paradigm for all the study participants. In order to compare pre-, immediately post-, and 6 months follow-up post intervention performance on the outcome measures all questionnaire and assessment data will be analysed using the SPSS General Linear Model procedure. Primary analysis will be done using simple t-statistics or chi-square statistics to evaluate differences between groups. Secondary analysis will involve explore the effect of moderators on working memory and decision-making. .

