### Strengths and limitations

This study has notable strengths. The trial will follow the gold-standard methodology in intervention research, i.e., double-blind, randomized-controlled, pre-registered with clinical trials registry, inclusion of active-control group, large sample size, and long duration of follow-up. There is limited research on DM, the relationship between WM and DM, and the efficacy of Cogmed in a paediatric TBI population. This study will address these gaps in the literature. DM deficits are typically assessed using tasks that are limited in their ability to replicate everyday functioning. A novel measure of DM has been developed in order to measure naturalistic decision-making processes in children. To our knowledge, this is the first trial investigating the impact of Cogmed on WM, DM, and functional outcomes in TBI population. The use of online training programs and online clinician support will ensure fewer burdens on families, higher participation, and adherence to training.

Predicted challenges of this study include recruitment of such a large sample size with respect to a screening component, ensuring participant adherence to training regardless of randomisation, and participant follow-up**.** Another limitation pertains to the blinding of participating families. While the research personnel responsible for screening participants and administering outcome assessments are completely blinded, it is not possible to completely blind the parents to the training programs.

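### The General Linear Model named for the three-visit comparison, in its natural repeated-measures form, does not fit the promise of intention-to-treat for all participants, and the per-visit t-tests close only part of the gap

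*Protocol article*

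**What the plan says.** All the relevant text is in the protocol article; no SAP is shown.

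- **Population** (Data analysis): "This RCT will follow the intention-to-treat paradigm for all the study participants".
- **Three-visit comparison** (Data analysis): the aim is stated as "In order to compare pre-, immediately post-, and 6 months follow-up post intervention performance on the outcome measures", and for this "all questionnaire and assessment data will be analysed using the SPSS General Linear Model procedure". The section does not say whether this is the repeated-measures form or a separate univariate model per visit.
- **Primary analysis** (Data analysis): "Primary analysis will be done using simple t-statistics or chi-square statistics to evaluate differences between groups". How these tests relate to the GLM is not explained.
- **Expected difficulty** (Strengths and limitations): the predicted challenges include "ensuring participant adherence to training regardless of randomisation, and participant follow-up".
- **Size** (section on participant flow and sample size): the plan reads "This study will recruit 74 eligible participants and randomize 37 participants each in the treatment group and the active-control group". No missingness rate appears in the readable text, and the participant flow figure is not shown.

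**The concern.** The section names both a population and a procedure, and the two fit badly. SPSS GLM in repeated-measures form deletes a child listwise if any one of the T1, T2 and T3 scores is absent. A child who finished training and was tested at T2, but did not return six months later, then contributes nothing to the T2 comparison in that model.

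Two things are at stake. The first is precision, because observed scores are thrown away in a trial of 37 per arm. The second is bias. The arms use different programs over 25 sessions, and the Randomization section accepts that allocation may become clear to families once training starts. Loss that differs by arm and depends on how the child is doing is therefore plausible.

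**Working it through.** **Inputs.** From the document: 37 per arm, a difference of 0.8 SD, significance level 0.05, power 0.80. Assumed, because the document gives no values: the missingness rates, a two-sided test, and a correlation of 0.7 between visits. T1 is measured before randomisation (Recruitment and allocation), so for the child's own tests loss is taken to occur at T2 and T3 only.

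**The plan's own figure.** The target is a "statistically significant difference of 0.8 SD between the treatment group and an active control group based on Automated Working Memory Assessment". At level 0.05 and power 0.80, the two-sided calculation gives 25 per arm (normal approximation) or 26 (t-test). It does not give 37. With 37 per arm, t-test power at 0.8 SD is 0.92. The gap would match an allowance of 1 − 26/37 = about 30% loss, but the readable text does not say so. This matters here only because it shows some slack in the sample size.

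**Children kept by listwise deletion.** With a fraction m missing at each of T2 and T3:

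- Independent loss: proportion kept = (1 − m)².
- Monotone dropout at the same rate (the same children miss both visits): proportion kept = 1 − m.

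| m at each visit | Kept, independent | Per arm of 37 | t-test power at 0.8 SD | Per arm if monotone |
|---|---|---|---|---|
| 10% | 0.90² = 0.81 | 30.0 | 0.86 | 33.3 |
| 15% | 0.85² = 0.72 | 26.7 | 0.82 | 31.5 |
| 20% | 0.80² = 0.64 | 23.7 | 0.77 | 29.6 |

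A t-test at one visit keeps 37 × (1 − m) children per arm: 33.3, 31.5 and 29.6. With unequal loss of 10% at T2 and 20% at T3, the t-tests keep 33.3 at T2 and 29.6 at T3. Listwise deletion keeps 26.6 (independent) to 29.6 (monotone), with power 0.82 to 0.86.

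**Bias, illustrative null case.** Assume no true effect, unit SD, and correlation 0.7 between every pair of visits. In the Cogmed arm only, T3 is missing with probability 0.4 if the T2 score is below the arm mean, which is 20% loss overall. For a standard normal score, the part below the mean contributes −0.399 to the expectation. Among Cogmed completers:

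- T2 mean = 0.4 × 0.399 / 0.8 = +0.20
- T3 mean = 0.7 × 0.20 = +0.14
- T1 mean = 0.7 × 0.20 = +0.14, so the baseline is shifted as well

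The control arm stays at 0. The spurious arm difference then depends on the contrast:

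| Contrast in completers | T2 | T3 |
|---|---|---|
| Raw difference | +0.20 | +0.14 |
| Adjusted for T1 (slope 0.7) | 0.20 − 0.7 × 0.14 = +0.10 | 0.14 − 0.7 × 0.14 = +0.04 |
| Change from T1 | 0.20 − 0.14 = +0.06 | 0.14 − 0.14 = 0 |

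The per-visit t-test at T2 uses all children seen at T2 and has no bias here. At T3 it uses the completers and carries the raw +0.14. Because dropout depends only on the observed T2 score, a likelihood-based model that keeps the T2 scores of children who drop out would be unbiased in large samples at both visits.

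**Direction.** In a second illustration, the true difference was 0.80 SD and T3 dropout depended on the T2 score. The raw T2 difference among T3 completers was 0.73 SD when low scorers dropped out in both arms, and 0.93 SD when this happened in the treated arm only. The bias can go either way.

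**The case against.** The strongest objection is that a reader might infer that the whole trial analysis is complete-case and drops any child who misses one visit. The document does not support that, for three reasons.

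- The named primary analysis is t or chi-square statistics. Applied at each visit, these use every child observed at that visit, so a child with T2 and no T3 stays in the T2 test.
- The words repeated measures do not appear. A univariate GLM per visit, for example T2 on arm and T1, drops a child only from the visit missed.
- Imputation before the GLM is possible, and rules for missing data are commonly left to an SAP or full protocol. Silence on imputation is therefore no fault of a journal article. Expected attrition may also be in the figure that is not shown.

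It can be added that intention-to-treat often means only that children are analysed in the arm assigned whatever their adherence, and neither method breaches that. A reader might also take +0.20 SD as the bias of the planned GLM. It is a raw completer difference; the arm-by-time test of a repeated-measures GLM rests on changes, where the same scenario gives +0.06 at T2 and 0 at T3.

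All of this stands as a limit on the point, but it does not remove it. The article chose a procedure for a three-visit comparison whose natural form discards partly observed children, and placed it next to a promise covering all participants. The t-tests also leave out every randomised child without the outcome, and they make no use of T1. Which children enter the main result depends on a relation between the two methods that the section does not fix.

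**Conclusion.** The point holds conditionally. If the GLM is run as repeated measures without imputation, that comparison rests on children with all three visits and does not deliver the stated population. The t-test primary analysis avoids this at T2, but it is unadjusted for T1 and still limited to children observed at each visit.

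Under assumed independent loss of 10 to 20% at each of T2 and T3, listwise deletion keeps about 30 to 24 of 37 per arm, with power at 0.8 SD falling from 0.92 to between 0.86 and 0.77. Fewer children are lost if dropout is monotone, and at T3 listwise deletion then does no worse than the t-test. In the illustrative null case the bias ranges from +0.20 SD (T2, raw) to 0 (T3, change from T1). That case is deliberately one-sided, and none of its rates come from the document.

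This is a method that fits its stated principle badly and can be improved at little cost. It is not a critical error, because the size depends on missingness that the document does not quantify and the primary tests are less affected than the GLM.

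**What to change.** For continuous outcomes, replace both the GLM and the unadjusted t-test with one linear mixed model for repeated measures (SPSS MIXED, REML):

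- Response: scores at T2 and T3. Fixed terms: arm, visit, arm × visit and the T1 score.
- Analysis set: every randomised child with any post-baseline value, in the arm assigned.
- Primary comparisons: the arm contrasts at T2 and at T3, named as such.
- One sensitivity analysis for children with no post-baseline value.

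Age and sex as covariates and the choice of covariance structure are optional. Chi-square tests can remain for categorical outcomes.

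If the sponsor prefers to keep the present methods, the minimum is to state the form of the GLM, how it relates to the t-tests, and how children missing T2 or T3 are retained, for example by multiple imputation.

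The cost is analysis wording and slightly more analysis work in the same software, with no change to trial conduct. The model relies on data being missing at random given the observed scores. A child without a T1 score would need separate handling. That should be rare for the child's own tests, which precede randomisation, but is possible for teacher forms returned by post.

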### Trial management

This RCT will be supervised by chief investigators CC and CG who will meet fortnightly to discuss the study status. They will also manage unexpected occurrences relating to the protocol or any unforseen adverse events. The RCH Ethics Committee and the Australian New Zealand Clinical Trials Registry will be notified if necessary. No harm, potential or actual, is anticipated as a consequence of participation in this study, but in case of severe distress to any study participant, appropriate clinical referrals will be made.

### Strengths and limitations

This study has notable strengths. The trial will follow the gold-standard methodology in intervention research, i.e., double-blind, randomized-controlled, pre-registered with clinical trials registry, inclusion of active-control group, large sample size, and long duration of follow-up. There is limited research on DM, the relationship between WM and DM, and the efficacy of Cogmed in a paediatric TBI population. This study will address these gaps in the literature. DM deficits are typically assessed using tasks that are limited in their ability to replicate everyday functioning. A novel measure of DM has been developed in order to measure naturalistic decision-making processes in children. To our knowledge, this is the first trial investigating the impact of Cogmed on WM, DM, and functional outcomes in TBI population. The use of online training programs and online clinician support will ensure fewer burdens on families, higher participation, and adherence to training.

Predicted challenges of this study include recruitment of such a large sample size with respect to a screening component, ensuring participant adherence to training regardless of randomisation, and participant follow-up**.** Another limitation pertains to the blinding of participating families. While the research personnel responsible for screening participants and administering outcome assessments are completely blinded, it is not possible to completely blind the parents to the training programs.

## Discussion

Impairments in WM and DM commonly occur following childhood TBI. Currently there is minimal literature and a poor evidence base regarding intervention in this area. It is essential that effective treatment options are made available. The expected outcome of this proposed study is that the Cogmed program will be shown to be effective in improving WM and DM, and will also lead to generalised improvements in functional skills in children post-TBI. Our team will play a key role in translating Cogmed into standard clinical care, schools, and community settings. However, if findings are not significant, it will still be significant in knowing that Cogmed may not be an effective intervention for this population, suggesting it may need to be adapted for implementation in this clinical group.

## Abbreviations

ADHD: Attention deficit hyperactivity disorder
AWMA-S: Automated working memory assessment-short
BRIEF-P: Behaviour rating inventory of executive function-parent
BRIEF-T: Behaviour rating inventory of executive function-teacher
CBCL: Child Behaviour Checklist
DM: Decision-making
EF: Executive function
FSIQ: Full scale intelligence quotient
HREC: Human resources ethics committee
MCRI: Murdoch Children’s Research Institute
PedsQL: Paediatric Quality of Life
RCH: Royal Children’s Hospital
RCT: Randomized controlled trial
SD: Standard deviation
SSIS-P: Social skills improvement system rating scales-parent
SSIS-T: Social skills improvement system rating scales- teacher
T0-T2: Data collection time points 0 to 2
TRF: Teacher Report Form
VPRS: Victorian paediatric rehabilitation services
WASI-II: Wechsler Abbreviated Scale of Intelligence- Second Edition
WISC-V: Wechsler Intelligence Scale For Children- Fifth Edition
WM: Working memory
WRAT-IV: Wide Range Achievement Test: Fourth Edition
